# Are Routine Radiographs Needed the Day After Open Reduction and Internal Fixation Surgery for Distal Radius and Ankle Fractures: Study Protocol for a Prospective, Open Label, Randomized Controlled Trial

**DOI:** 10.2196/resprot.7698

**Published:** 2017-08-16

**Keywords:** wrist fracture, distal radius fracture, ankle fracture, postoperative radiograph, functional outcome, cost reduction, radiation exposure

## Abstract

**Background:**

Distal radius and ankle fractures are one of the most common operatively treated fractures. To date, there is no consensus concerning the need for a standard postoperative radiograph. This leads to undesirable practice variations. A standardized radiograph in the department of radiology would theoretically be more reproducible and operator independent than an intraoperatively obtained fluoroscopic image. However, if adequate intraoperative radiographs have been obtained, it is questionable if these postoperative radiographs are necessary and will lead to changes in the treatment strategy. If standard postoperative radiographs are no longer required, this would lead to a reduction in radiation exposure and health care costs. The hypothesis is that routine standardized postoperative radiographs do not influence the quality of care for patients operated on for either a distal radius or an ankle fracture if adequate intraoperative standardized radiographs have been obtained.

**Objective:**

The primary aim of this study is to evaluate if there is a need for routine postoperative radiographs after an osteosynthesis of a distal radius or ankle fracture.

**Methods:**

In a prospective, randomized controlled, open label trial based on a noninferiority design, we will enroll 332 patients. Patients will be randomized either in the control or the intervention group. The control group will be treated according to our current, standard protocol in which all patients receive a standard anterior-posterior and lateral radiograph on the first postoperative day. Patients randomized to the intervention group will be treated without a standard postoperative radiograph. All patients (N=332) will have a routine clinical and radiographic control after 6 weeks in the outpatient clinic. Primary outcome is a change in treatment plan, defined as either additional imaging or a reoperation based on the postoperative imaging. Secondary outcome measures include a 36-Item Short Form Survey, Patient-Rated Wrist Hand Evaluation, Foot and Ankle Outcome Score, Visual Analogue Scale, and the range of motion. Those questionnaires will be filled out at the 6-week outpatient control.

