### Rationale

Intraoperative radiograph documentation, if standardized and adequately performed, has the potential to assess the quality of reduction and fixation [3,4]. Consequently, the additional value of routine postoperative radiographs should be questioned [5].

Given the trend towards cost-effective medicine [6] and keeping cumulative radiation exposure in mind, it is not surprising that these standardized postoperative radiographs are under debate [8]. Despite the above, routine postoperative radiographs are still being performed in many hospitals as a standard of care. Many surgeons and radiologists argue that radiographs obtained in the department of radiology are more standardized and less biased. We therefore evaluated the frequency of changes in treatment plan due to standardized postoperative radiographs in a retrospective trial. Changes in treatment plan were defined as a deviation from the standard postoperative protocol. This included additional imaging or a revision operation.

We found in 7.2% of patients a change in the treatment plan following the evaluation of the standardized postoperative radiograph for patients operated on for distal radius or ankle fractures in 2014. These numbers are high in percentage and suggest that standardized postoperative radiographs do add to the quality of care for the patient.

On the other hand, this retrospective study had several methodological drawbacks, especially as the intraoperative radiographs performed were not standardized. Therefore, we decided to evaluate the need for postoperative radiographs using a prospective randomized control trial. We would expect a significant reduction in radiation exposure and costs of around CHF 1.3 million (estimated for employed patients in Switzerland in 2015 [9]).

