#### Primary Outcome

We defined the primary outcome as any re-intervention or necessity for additional imaging due to insufficient intraoperative imaging or achieved reduction.

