### Statistical Analysis

Statistical analysis will be carried out using SPSS, IBM Version 21. In order to answer the primary research questions, the number of re-interventions will be compared between both groups. Additionally, we will use regression *models* to try to identify risk factors for these re-interventions such as timing and duration of surgery and the experience of the surgeon.

In order to address the secondary research questions, the evaluated specific and nonspecific outcome scores will be compared between the two groups using means and standard deviation.

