### Sample Size Calculation

We determined the sample size for both the radius and ankle fracture group after a retrospective evaluation concerning the rate of postoperative treatment plan changes. We found a rate of 7.2% changes in treatment plan after obtaining standard postoperative radiographs in 2014. Based on these findings and using a power of 0.80 and alpha failure of .05, we performed a sample size calculation.

Based on a noninferiority approach, we calculated 158 patients needed in each treatment arm. Corresponding to the standard protocol following operative fracture care, we have a standard first outpatient control after 6 weeks. Based on a separate evaluation, concerning the frequency of patients being lost to follow-up, 4.6% of our patients in 2014 did not obtain their 6-week control. Therefore we added 5% loss of follow-up to our power calculation, resulting in 158 x 1.05=166 patients in each treatment arm.

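### The primary outcome is stated three ways, and on each of them an event does not mean the same thing in the two arms because detection depends on the radiograph being withheld

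*Protocol article*

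**What the plan says.** The protocol article describes the primary event in three places.

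- **Abstract, Methods:** "Primary outcome is a change in treatment plan, defined as either additional imaging or a reoperation based on the postoperative imaging".
- **Methods, Primary Outcome:** "We defined the primary outcome as any re-intervention or necessity for additional imaging due to insufficient intraoperative imaging or achieved reduction".
- **Methods, Statistical Analysis:** for the primary question, "the number of re-interventions will be compared between both groups". Additional imaging is not named.

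Imaging differs by arm. In the control arm "all patients receive a standard anterior-posterior and lateral radiograph on the first postoperative day", whereas "Patients randomized to the intervention group will be treated without a standard postoperative radiograph". Both arms share a later film: "All patients (N=332) will have a routine clinical and radiographic control after 6 weeks in the outpatient clinic".

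The Inclusion Period section has a senior surgeon and a senior radiologist assess the intraoperative images the next day. The Intervention Group section adds that poor images or a poor reduction lead to further imaging or a revision.

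The sample size rests on one rate: "We found a rate of 7.2% changes in treatment plan after obtaining standard postoperative radiographs in 2014". The Rationale defines such changes as additional imaging or revision, and comments that the figures "suggest that standardized postoperative radiographs do add to the quality of care for the patient".

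**The concern.** In a noninferiority comparison of event counts, an event must be a bad outcome and must have the same chance of being found in each arm. Here the withheld test is itself a main source of events.

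Under the Abstract wording, a poor reduction found on the day-1 film is a control-arm event. The same defect in the intervention arm, if the intraoperative images do not show it, counts only when something else reveals it, such as the 6-week film. The Rationale treats these findings as a possible benefit of the radiograph, yet the comparison scores them as control-arm failures.

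At stake is whether a declaration of noninferiority would mean that omission is safe, or only that fewer problems were looked for.

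**Working it through.** **1. The three definitions side by side**

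| Source | Event | Control arm | Intervention arm |
|---|---|---|---|
| Abstract | Change based on postoperative imaging | Day-1 film, 6-week film | No routine day-1 film; 6-week film, or imaging prompted by review |
| Primary Outcome | Re-intervention or extra imaging because intraoperative images or reduction were inadequate | The routine film may supply the missing imaging without an event | Extra imaging after review is an event |
| Statistical Analysis | Re-interventions only | Can be prompted by the day-1 film | Can be prompted by review or later findings |

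The first row tilts towards the intervention arm. The second can tilt against it. How far depends on what happens to patients with poor intraoperative images. Study Population excludes those whose standardized images were missed, and Inclusion Period keeps a patient in the assigned arm if the images are good. Intervention Group instead describes further imaging or revision for such patients. If they leave the study, the second-row counterweight largely goes and the Abstract bias dominates. The third row also does not match the sizing rate, because 7.2% includes additional imaging.

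**2. The sample size**

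Inputs from Sample Size Calculation: rate 7.2%, power 0.80, alpha 0.05, 158 per arm. The article gives no margin, sidedness or intervention rate, so 158 cannot be reproduced directly. Assuming equal true rates, the implied margin is

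d = sqrt[ 2p(1−p)(z₁₋α + z₀.₈₀)² / n ]

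- One-sided 0.05: sqrt[2 × 0.072 × 0.928 × (1.645 + 0.842)² / 158] = 0.0723. A margin of exactly 7.2 points gives 160 per arm.
- One-sided 0.025: the same formula with 1.960 gives 0.0815.

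The dropout step reproduces: 158 × 1.05 = 165.9, so 166 per arm and 332 in total.

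**3. Probability of declaring noninferiority**

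This is an exact enumeration of two binomials, 158 per arm, control rate 7.2% (158 × 0.072 = 11.4 expected events). Noninferiority is declared when the Agresti-Caffo upper limit for intervention minus control lies below the margin. All margins and intervention rates are assumptions.

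| Intervention rate | 7.23 points, one-sided 0.05 | 8.15 points, one-sided 0.025 | 5 points, one-sided 0.05 | 3 points, one-sided 0.025 |
|---|---|---|---|---|
| 0% | 1.00 | 1.00 | 1.00 | 1.00 |
| 2% | 1.00 | 1.00 | 0.998 | 0.944 |
| 5% | 0.966 | 0.966 | 0.843 | 0.460 |
| 7.2% | 0.793 | 0.786 | 0.519 | 0.165 |
| 10% | 0.406 | 0.389 | 0.170 | 0.028 |
| 14.4% | 0.054 | 0.047 | 0.012 | 0.001 |

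**4. Direction**

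Hold the intervention rate at 5% (margin 7.23 points, one-sided 0.05) and let the day-1 film find more in the control arm. Control rates of 3.6%, 7.2%, 10% and 14.4% give probabilities of 0.79, 0.97, 0.99 and 1.00. The more the radiograph finds, the easier it is to conclude that it can be dropped.

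**The case against.** The strongest reply is that the Methods definition, not the Abstract, should govern. It is not tied to postoperative imaging. The next-day review gives the intervention arm a real route to early events, so a malreduction visible on the intraoperative images can be acted on and counted. Removing patients with poor images would not remove those whose good images show a poor reduction. The Rationale also cautions that intraoperative images were not standardized in the retrospective study, so the authors do not take 7.2% as proof of benefit. Function, pain and complications are assessed at 6 weeks in both arms.

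Much of this stands. A reader might infer that noninferiority is close to guaranteed, or that the trial cannot answer its question at all. The documents do not support either. The first needs an intervention rate near 0-2%, which the article nowhere gives and which the review route makes uncertain. The second ignores the secondary outcomes, which could show harm from omission.

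The reply does not make the event comparable between arms. The Inclusion Period section does not limit next-day review to one arm, so the day-1 film remains an extra chance of detection in the control arm. Where review prompts additional imaging, the Primary Outcome wording brings in an asymmetry of the opposite sign.

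**Conclusion.** The point holds: there are three differing statements of the primary outcome, and on each of them ascertainment depends on the arm. Under the Abstract wording, and for the rate used in sizing, the bias is towards noninferiority. Under the Primary Outcome wording its direction is open.

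At the inferred margin of about 7.2 points (one-sided 0.05, 158 per arm, control 7.2%), the probability of declaring noninferiority runs from about 1.00 at an intervention rate of 0-2% to 0.41 at 10%. That spread can come from how events are found and defined, with no difference in surgical quality between the arms. The margin and the intervention rates are assumptions; the unequal ascertainment follows from the text alone. Because it affects the primary comparison, it should be settled before analysis.

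**What to change.** Reconcile the Abstract, Primary Outcome and Statistical Analysis sections into one primary event:

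- unplanned re-intervention for reduction or implant position, or unacceptable reduction or implant position on the scheduled 6-week radiograph, judged against the predefined standards to which the Intervention Group section refers;
- counted from surgery to the 6-week visit, whatever triggered it;
- with the 6-week film read without knowledge of arm where the existing readers allow.

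Report changes triggered by the day-1 film descriptively, as control-arm yield. Make additional imaging a secondary process outcome. Reconcile Study Population, Inclusion Period and Intervention Group on whether patients with inadequate intraoperative images stay in the study and the analysis. State the margin, and restate the power at the current N=332 over a range of event rates.

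**Cost:** an outcome amendment and a new power statement, with no new visit or procedure because the 6-week film is already planned for everyone. The new event rate is less well known than 7.2%, so the stated power is less certain. The primary outcome would also change after at least 104 patients were enrolled, so the amendment should be dated and its reason given.

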**Results:**

The trial was started in August 2016, and 104 patients have been enrolled up to this point.

**Conclusions:**

Our findings will be reported in peer-reviewed publications and may lead to a strong reduction in radiation exposure and health care costs. A preliminary, conservative estimation suggests a yearly cost saving of CHF 1.3 million in Switzerland.

## Introduction

In a society that is increasingly demanding about the functional outcome after treatment of fractures, the indications for operative treatment have increased over the past decade. Wrist fractures specifically are more often being treated operatively. In addition, due to an increase in the number of patients with obesity, the numbers of patients treated for ankle fractures are also increasing [1,2].

Many hospitals still use routine postoperative radiographs, despite the fact that intraoperative images have been obtained for reduction and implant control. In addition, these images are stored and available in the Picture Archiving and Communication System (PACS). These postoperative radiographs lead to a significant increase in radiation exposure and costs. It remains questionable if these standard postoperative radiographs are justified since the quality of intraoperative C-arm images has improved over the last decade.

### Rationale

Intraoperative radiograph documentation, if standardized and adequately performed, has the potential to assess the quality of reduction and fixation [3,4]. Consequently, the additional value of routine postoperative radiographs should be questioned [5].

Given the trend towards cost-effective medicine [6] and keeping cumulative radiation exposure in mind, it is not surprising that these standardized postoperative radiographs are under debate [8]. Despite the above, routine postoperative radiographs are still being performed in many hospitals as a standard of care. Many surgeons and radiologists argue that radiographs obtained in the department of radiology are more standardized and less biased. We therefore evaluated the frequency of changes in treatment plan due to standardized postoperative radiographs in a retrospective trial. Changes in treatment plan were defined as a deviation from the standard postoperative protocol. This included additional imaging or a revision operation.

We found in 7.2% of patients a change in the treatment plan following the evaluation of the standardized postoperative radiograph for patients operated on for distal radius or ankle fractures in 2014. These numbers are high in percentage and suggest that standardized postoperative radiographs do add to the quality of care for the patient.

On the other hand, this retrospective study had several methodological drawbacks, especially as the intraoperative radiographs performed were not standardized. Therefore, we decided to evaluate the need for postoperative radiographs using a prospective randomized control trial. We would expect a significant reduction in radiation exposure and costs of around CHF 1.3 million (estimated for employed patients in Switzerland in 2015 [9]).

### Hypothesis

Our hypothesis is that routine standardized postoperative radiographs do not influence the quality of care for patients operated for a distal radius or ankle fracture if adequate intraoperative standardized radiographs have been obtained.

This is the first prospective randomized trial evaluating the additional value of postoperative routine radiographs in operative fracture care of distal radius and ankle fractures.

Human research ethics approval has been obtained from the Ethikkomission Nordwest- und Zentralschweiz (EKNZ). The commission accepted this trial on April 4, 2016 (EKNZ BASEC 2016-00114).

## Methods

Based on a noninferiority design, we planned a prospective, randomized controlled, open label trial. Multimedia Appendix 1 shows the study protocol in accordance with the Standard Protocol Items: Recommendations for Interventional Trials (SPIRIT) checklist [10].

### Study Population

The study includes patients operated for a distal radius or ankle fracture at a Level 1 trauma center in Switzerland. Patients presenting with these fractures at the emergency department will be eligible for study inclusion if they fulfill all of the following criteria: indication for an operation of a distal radius fracture, according to the Arbeitsgemeinschaft für Osteosynthesefragen (AO) Classification types 23-A-C [4], or an ankle (according to the AO Classification Types 44-A-C) fracture, 18 years of age or older, sufficient understanding and writing of German language, and signed informed consent. The informed consent forms will be stored by the study nurse during the trial.

Patients are excluded if they meet at least one of the following exclusion criteria: not willing/able to sign the informed consent, indication for postoperative computed tomography (CT), pathological fractures, open fractures (>grade I according to Anderson and Gustilo [11]), patients not able to attend the 6 weeks outpatient control, or missed intraoperative standardized radiographs.

### Preliminary

Essential pre-study preparations are needed to ensure standardization of intraoperative C-arm handling, limb positioning, and reproducibility of the collected data.

#### Defining Period

Standard intraoperative radiographs for patients operated for radius fractures are defined as:

anterior-posterior and posterior-anterior radiograph of the wrist with a free visualization of the distal radio-ulnar space (defined as no overlap of distal radius and distal ulnar)20° radial tilted lateral view in which the os pisiform needs to have an overlap with the scaphoid and the ventral cortex of the lunatetangential view [12,13]

Sufficient standard intraoperative radiographs are shown in Figures 1,2, and 3.

Standard intraoperative radiographs for patients operated for ankle fractures are defined as:

anterior-posterior view (mortise view) with cleared space between trochlea tali and the tibia/fibula (achieved by inward rotation of 20°)true lateral view with an overlap of the medial and lateral domes of the talus and the fibula forming the posterior one-third of the tibia

Sufficient standard intraoperative radiographs are shown in Figures 4 and 5.

**Figure 1 figure1:**
[figure not shown]
Intraoperative C-arm controlled radiograph (anterior-posterior) in supination with cleared radio-ulnar space.

**Figure 2 figure2:**
[figure not shown]
Lateral view with free os pisiforme on the volar level and intra-articular view.

**Figure 3 figure3:**
[figure not shown]
Intraoperative tangential view performed to evaluate the length of the screws.

**Figure 4 figure4:**
[figure not shown]
Intraoperative C-arm control: the ankle is shown in anterior-posterior view, free mortise view is achieved with 90° dorsal extension and 20° rotation inside.

**Figure 5 figure5:**
[figure not shown]
Intraoperative C-arm control: the ankle is shown in a lateral view, to show the trochlea tali for intra-articular view; the fibula forms the posterior one-third of the tibia.

#### Implementation Period

An educational period teaching standard intraoperative radiographs will be initiated before the inclusion period starts. All trauma surgeons treating the above mentioned fractures will participate in a special lecture about standardization of intraoperative radiographs. Additionally, a tailored personal instruction lecture by the senior surgeon will be initiated.

In a last educational step, personal hand-outs, providing information about appropriate standardization, are given to each trauma surgeon as well as a special lecture involving the residents and interns who participate in orthopedic trauma surgery. They are informed about the necessity of a signed informed consent as the surgeon at the emergency department is responsible for the inclusion.

#### Inclusion Period

After sufficient information is provided to all trauma surgeons, inclusion starts. Intraoperative radiographs are obtained by the ZIEHM SOLO (Ziehm Imaging GmbH). These radiographs are saved separately in our PACS. The next day, these radiographs are evaluated by the senior surgeon of the department of orthopedics and trauma surgery and a senior radiologist. If the quality of the intraoperative radiographs is standardized and good, the patient remains in the study arm to which they were assigned.

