### Randomization

Prior to the operation, the patients are randomized to the control or the intervention group. The randomization will be carried out using a special in-hospital randomization tool. Thereafter, the patient will be included in one of the following two groups.

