#### Intervention Group (Group II)

Patients belonging to the intervention group will have a modified postoperative protocol. After interdisciplinary consensus (between the head of the orthopedics department and trauma surgery and radiology) that the quality of the intraoperative radiographs are performed in a standardized fashion with good quality and that the reposition is within the predefined standards, patients will be mobilized according to our routine postoperative protocol and will be reviewed in our outpatient department after 6 weeks (clinically and radiologically).

If the quality of the intraoperative radiographs or the reduction is not acceptable, additional imaging (plain radiographs or CT) or a revision operation is performed.

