### Strengths and Limitations

This randomized trial will provide prospective data for a common health care problem and the appropriate aftercare. Due to its randomized design, this trial will provide high-quality evidence with clearly predefined objective results.

Outpatient control, for all patients 6 weeks postoperatively, performed by a specialized (orthopedic) trauma surgeon ensures comparable and objective analysis in terms of early surgical outcome.

As a secondary outcome measurement, functional analysis using validated questionnaires will provide additional information. If this trial demonstrates comparability in terms of quality in aftercare between both groups, this could be the basis for a change in standard postoperative process with savings in radiation exposure and health care costs.

Limitations of this study are the single-center design and the lack of blinding during the study period.

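### Image adequacy is judged after randomization and serves both as a condition for staying in the trial and as a primary-outcome event, with no rule saying which applies

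*Protocol article*

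**What the plan says.** All places are in the Protocol article.

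- **Randomization:** "Prior to the operation, the patients are randomized to the control or the intervention group". No intraoperative image exists at that point.
- **Study Population** ends its list of exclusion criteria with "patients not able to attend the 6 weeks outpatient control, or missed intraoperative standardized radiographs".
- **Inclusion Period:** "The next day, these radiographs are evaluated by the senior surgeon of the department of orthopedics and trauma surgery and a senior radiologist". It continues: "If the quality of the intraoperative radiographs is standardized and good, the patient remains in the study arm to which they were assigned". The consequence of images that are not good is not stated there.
- **Intervention Group (Group II):** "If the quality of the intraoperative radiographs or the reduction is not acceptable, additional imaging (plain radiographs or CT) or a revision operation is performed".
- **Primary Outcome** is defined as "any re-intervention or necessity for additional imaging due to insufficient intraoperative imaging or achieved reduction".
- **Control Group (Group I):** every patient has a routine radiograph in the radiology department. The Abstract places it on the first postoperative day.
- **Strengths and Limitations:** "Limitations of this study are the single-center design and the lack of blinding during the study period".
- **Sample Size Calculation:** 158 per arm, raised to 166 by adding 5% for loss to follow-up. No noninferiority margin is stated.

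**The concern.** Image adequacy plays two incompatible roles. Under Study Population and Inclusion Period it governs whether a randomized patient stays. Under the Intervention Group and Primary Outcome sections, inadequacy that leads to more imaging or to revision is the event the trial counts. Nothing ranks these rules.

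The arms are not symmetric on this point. A control patient with poor intraoperative images has the routine day-1 radiograph regardless, so nothing *additional* need be ordered. An intervention patient with the same images is sent directly to additional imaging or revision. Removing patients with poor images would therefore tend to delete more events from the intervention arm than from the control arm. In a noninferiority trial that pushes towards the conclusion the sponsor hopes for. The reviewers who decide know, or can know, the allocation.

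**Working it through.** **The rules applied to one patient.** Take an intervention patient whose intraoperative images are judged inadequate the day after surgery.

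| Section | Reading |
|---|---|
| Study Population | Excluded, if the images count as missed |
| Inclusion Period | Does not meet the condition for remaining in the arm; consequence unstated (removal or change of arm both possible) |
| Intervention Group | Stays, and has additional imaging or revision |
| Primary Outcome | Counted as an event |

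The first two rows and the last two cannot all govern the same patient.

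**The plan's own figures.** 158 × 1.05 = 165.9, so 166 per arm, and 2 × 166 = 332. These reproduce. The 158 cannot be uniquely reproduced, because neither the margin nor the sidedness of alpha is given. With a rate of 7.2% in both arms and power 0.80, the implied margin is

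m = √(2 × 0.072 × 0.928 / 158) × (z(1−α) + 0.842).

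- One-sided α = 0.05: m = 0.02908 × 2.486 = 0.0723, or 7.23 points.
- One-sided α = 0.025: m = 0.0815, or 8.15 points.

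A two-sided superiority comparison of 7.2% with 1.0% gives 160 per arm, so even the type of calculation is not settled by the figure.

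**Illustration of what the choice of rule can do.** Assumptions not in the documents:

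- a share q of intervention patients fails the image review;
- each such patient is an event, and the rest have a 7.2% rate;
- the control rate is 7.2%;
- m = 0.0723 at one-sided 0.05.

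Intervention rate if failures are counted: p₂ = q + (1 − q) × 0.072.

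P(noninferior) = Φ[(m − (p₂ − 0.072)) / √((0.072 × 0.928 + p₂(1 − p₂)) / n) − 1.645].

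At q = 5% and n = 158: p₂ = 0.05 + 0.95 × 0.072 = 0.1184, the excess is 0.0464, and the standard error is 0.0329. The result is Φ(0.787 − 1.645) ≈ 0.20.

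If failures are removed from both arms at the same rate, n = 158 × 0.95 = 150.1, the difference is 0, and the result is 0.78.

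| q | Excess if counted in the intervention arm only | P(noninferior), counted | P(noninferior), removed |
|---|---|---|---|
| 2% | 1.9 points | 0.54 | 0.79 |
| 5% | 4.6 points | 0.20 | 0.78 |
| 10% | 9.3 points | 0.01 | 0.76 |

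With the 8.15-point margin at one-sided 0.025 the pairs are 0.54/0.79, 0.19/0.78 and 0.01/0.76, so the pattern does not depend on which margin was meant. The excess reaches the 7.23-point margin at q = 0.0723/0.928 = 7.8%.

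**Failures counted equally in both arms.** At q = 5% both rates are 0.1184. The standard error is √(2 × 0.1184 × 0.8816 / 158) = 0.0363, and power is Φ(0.0723/0.0363 − 1.645) ≈ 0.63. At q = 10% it is about 0.53. The difference is then zero, but the higher event rate costs power.

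**Erosion of numbers.** With 5% lost and an assumed 10% excluded, 166 × 0.95 × 0.90 = 141.9, or about 142 per arm. Power is Φ(0.0723/√(2 × 0.072 × 0.928 / 142) − 1.645) ≈ 0.76, against 0.80 at 158.

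**The case against.** The case on the other side has substance.

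- *The plan does not say that patients with poor images are excluded.* A reader might infer that it does, but Inclusion Period states only who remains, and missed images may mean images never taken. The only explicit handling of poor images is the Intervention Group pathway, which keeps the patient. This stands. Even so, the narrow reading still removes randomized patients for something that happens in theatre, and leaves the outcome of the next-day review undefined.
- *The hypothesis is limited to patients with adequate intraoperative images, so restricting to them is intended.* The Abstract and the Hypothesis section do say this. But that target population calls for randomization after the review. It would also largely empty the part of the primary outcome that concerns insufficient imaging.
- *Equal removal in both arms need not bias the comparison.* Correct. Bias needs unequal review, unequal image-taking or unequal event creation. The day-1 radiograph in one arm only makes the last plausible, and open-label review makes the first possible. The documents show neither as fact.
- *A postoperative CT indication is also an exclusion.* A reader might infer that it, too, can be known only after surgery. The text gives no timing, and an indication set before surgery fits equally well. Only indications that arise after randomization belong to this point.
- *Analysis sets are usually left to the full protocol or analysis plan.* True, but the point is the conflict between eligibility, retention and outcome rules that are printed in the article.

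**Conclusion.** The point holds as a conflict of stated rules. Randomized patients with inadequate images can be read as removed, moved or counted as events, and the choice is related to the outcome and made open label. This needs to be settled before the primary comparison can be computed unambiguously.

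The direction of the risk is towards noninferiority if intervention-arm failures are removed. The documents do not support saying that the randomized comparison is already broken, or that the choice of reading will decide the result. No inadequacy rate and no margin are given, and the contrast of 0.20 with 0.78 at a 5% failure rate rests on an assumed rate, a back-solved margin and counting in the intervention arm only. The loss of power from exclusions is minor: about 76% against 80% with 5% lost and 10% excluded.

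**What to change.** Reconcile the Study Population, Inclusion Period, Intervention Group and Primary Outcome sections on how such patients are retained and counted:

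1. Do not apply image adequacy, or a CT indication that arises after randomization, as an exclusion for patients already randomized.
2. Make the primary analysis all randomized and operated patients in their assigned arm.
3. State one rule, for both arms, for when inadequate images or reduction count as an event, including how the control arm's routine day-1 radiograph is treated under it.
4. Keep adequate-images-only as a secondary analysis set, and report inadequacy by arm.

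Alternatively, if the target population really is patients with adequate images, randomize the remaining patients after the next-day review. Review and routine radiograph fall on the same day, so allocation would have to come between them.

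Costs: an amendment, which under Ethical Considerations needs ethics committee approval; tracing of any patients already dropped among the 104 enrolled, whose 6-week visit is routine; and possibly a less favourable intervention event rate. The stated power should be rechecked once the event rule is fixed, since counting failures in both arms raises the event rate and lowers power at 158 per arm.
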